### Procedure for unblinding if needed {17b}

Unblinding of the treatment will only be initiated by the Data Safety Monitoring Board (DSMB) on an individual basis in the event of a consistent occurrence of serious adverse events potentially related to the study treatment, raising concerns about potential harm. Causality will be determined through discussions between the principal investigators (PIs), the study clinician with input from the local safety monitor (LSM). Throughout the unblinding process, the interpretation of the intervention codes will not be documented in any paperwork accessible to the blinded team unless absolutely necessary. If documentation in accessible paperwork is unavoidable, the assumption of complete unblinding for that participant will be made.

### Relevant concomitant care permitted or prohibited during the trial {11d}

Participants who are planning to use any vitamin supplements during the trial will be excluded from enrolment. Once enrolled, participants will only be prescribed with vitamins by the research clinician when deemed necessary.

### Assessments {18a}

#### Laboratory and clinical evaluations {33}

At both baseline (day 0) and at the endline (day 84), 0.5 ml and 3.0 ml of venous blood will be collected into EDTA (BD Microtainer, K2E, REF; 365975, USA) and serum separator tubes (BD vacutainer, REF;367957, UK). Parents/guardians will be provided with baby diapers and instructed to use them to collect stool in the mornings before the baseline and endline visits. Blood samples will be processed within 4 h after collection by trained lab personnel in a GCLP-accredited laboratory. The EDTA samples will be used to assess the full blood count and reticulocyte markers using an automated haematology analyser (Sysmex XN-Series 1500, Sysmex Corporation, Japan). The serum samples will be stored at − 80 °C until subsequent analysis of iron status markers (ferritin, transferrin, transferrin saturation, unbound iron-binding capacity, soluble transferrin receptor) and inflammatory markers [C-reactive protein (CRP) and α-1-acid glycoprotein (AGP)] using a Cobas Integra 400 plus (Roche Diagnostics, Rotkreuz, Switzerland). ELISAs will be used to measure serum concentrations of hepcidin (DX-EIA-5782, DRG, Germany), erythropoietin (DX-EIA-3646, DRG, Germany) and erythroferrone (ERF-001, Intrinsic Lifescience LLC, USA).

Faecal samples from the diapers will be collected and placed into a container and placed on ice. The samples will be transported to the Keneba Laboratory. Stool will then be assessed for calprotectin (MRP 8/14, DX-EIA-5415, DRG, Germany), myeloperoxidase (in-house ELISAs) and gut pathogens (in-house DNA analysis).

Additionally, anthropometric measurements (weight and height at baseline and endline), vital signs, adverse events and qualitative data such as screening, demography, daily iron supplement and weekly feeding questionnaires will be collected. All laboratory analysis results will be captured electronically in the REDCap project database. The blood and faecal samples collected during the trial may be used to support other research in the future and may be shared anonymously with other researchers, for their ethically approved projects. Any future use of data or samples will require approvals from the principal investigator, MRCG@LSHTM Scientific Coordinating Committee, and Ethics Committee.

### Adverse event assessment and reporting {11b}

All adverse events and serious adverse events will be recorded by the research clinician or nurses in RedCap and treatment/referral provided where required. Bi-weekly meetings with the field team will be held and a summary of field activities including the number of participants who consented, screened and any adverse events reported. Field workers will immediately call the research clinician/study nurse if they find a participant is unwell and will seek advice if the investigational product should be withheld. Reported fever will be confirmed by measuring the axillary temperature using a digital thermometer in the field by field workers. The outcome will be reported to the clinical team immediately who will decide on treatment/clinical referral where required. All symptoms or signs reported or observed will be documented after evaluation by the study nurse or clinician.

Investigational products shall be withheld for 7 days following the detection of the following conditions: (1) confirmed fever (axillary temperature > 37.5 °C) not associated with teething or vaccination, (2) visually confirmed bloody diarrhoea, (3) hospitalisation for somatic illness and (4) treatment with antibiotics for any confirmed or suspected infection.

#### Adverse event reporting and harms {22}

Adverse events whether related or unrelated to the interventions will be captured. These will include respiratory tract infections (including upper respiratory tract infections, pneumonia and bronchiolitis), gastrointestinal (gastroenteritis, acute watery diarrhoea, persistent diarrhoea and bacillary dysentery) and skin infections (skin infection, abscess and conjunctivitis) (Additional file 4_Adverse Event eCRF). Diarrhoea will be defined as three or more fluid stools as reported by parents/guardians within the previous 24-h recall period [11]. Acute watery diarrhoea will be defined as diarrhoea that lasts several hours or days [11]. Persistent diarrhoea will be defined as diarrhoea that lasts 14 days and longer with three of more days between episodes [11].

### Data management {19}

Only those individuals who have received training on the CRF/eCRFs and/or other document completion and have been authorised by the principal investigator will complete CRFs and other study-specific documentation. The study data collected on the eCRFs will be captured using devices, i.e. tablets and/or laptops, used by the study staff. Quality control checks will be conducted by the data manager (DM) as data is received. Any missing data identified will result in queries being assigned to the respective data collectors for correction. An internal monitor will oversee the study to ensure data quality and compliance with the International Council for Harmonisation of Technical Requirements for Pharmaceuticals for Human Use (ICH GCP) standards.

The database locking process will be initiated when the study reaches its predefined closure time. The database will be thoroughly reviewed, cleaned and checked by the data manager and their team. Once the database is ready for locking, user access will be removed, and a backup copy will be sent to the Archive Department. The data manager and statistician will be responsible for executing the database locking process, ensuring data completeness and accuracy before statistical analysis. The final data format can be exported to Excel and commonly used statistical packages such as SPSS, SAS, Stata and R.

### Outcome measures {12}

The primary and secondary outcomes will be collected at baseline (day 0) and endline (day 84) at the study sites. The *primary endpoints* are haemoglobin concentration and serum ferritin concentration at day 84. Secondary endpoints related to the primary objective will include proportion of children with anaemia (haemoglobin concentration < 11.0 g/dL) [12] at study day 84, proportion of children with iron deficiency (ID) (ferritin < 12 μg/L or < 30 μg/L in the presence of inflammation) [13] and proportion of children with iron deficiency anaemia (IDA) (haemoglobin concentration < 11.0g/dL and sTfR mg/L/logFerritin ratio > 2.0, ferritin < 30 μg/L in the presence of inflammation (CRP > 5 mg/L)) [14] at day 84. We will also determine other haematology (MCV, MCH, MCHC, reticulocyte-haemoglobin concentration and reticulocyte count) and iron status markers (iron, transferrin, soluble transferrin receptor, hepcidin, erythropoietin, erythroferrone, transferrin saturation, unbound iron binding capacity) at day 84. We will also measure the effect of the intervention on growth.

Safety measures will consist of the incidence of adverse events and serious adverse events per child over the observation period and serum concentrations of inflammatory markers (C-reactive protein/α1-acid glycoprotein) at day 84 and faecal calprotectin.

### Statistical plan

#### Sample size determination {14}

The sample size was determined by the primary endpoints, haemoglobin concentration and serum ferritin concentration, which will both be measured 84 days after randomisation (Fig. 2) using Microsoft Excel™ with a 5% dropout rate; a total of 208 children will be randomised, which will be sufficient to (a) provide 90% probability that, if the real group difference in haemoglobin concentration is 5.0 g/L or more, the 95% CI for the difference would exclude 0 [calculation based on the assumption that the SD for haemoglobin is 10g/L for each group (estimate based on previous experience in many previous trials in African children)] and (b) have 90% probability that, if the real change of the geometric mean serum ferritin concentration in the haem group iron relative to the control group is 75% or more, the 95% CI for the ratio would exclude 0 [calculation based on the additional assumption that the variance of log_e_-(serum ferritin concentration, μg/L) equals 1.232 for each group [15]].

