## Methods/design {8}

### Study design

This will be a 2-arm parallel randomised controlled superiority trial, with participants, field staff outcome assessors and biostatisticians blinded to the treatment arm. The trial will be conducted in rural Gambia, and potential participants will be recruited from vaccination clinics or their communities. A total of 208 participants will be randomised to either haem iron or ferrous sulphate using a 1:1 allocation ratio and supplemented daily for 84 days (Fig. 2).

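### The ferritin power statement uses the wrong null value for a ratio, and the printed inputs call for about 175 to 182 children at 90% power, not 208

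*Protocol article*

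**What the plan says.** The section Sample size determination {14} names haemoglobin and ferritin at day 84 as the endpoints that determined the size. The calculation was done "using Microsoft Excel™ with a 5% dropout rate", and "a total of 208 children will be randomised". Study design gives the same total and has the children "randomised to either haem iron or ferrous sulphate using a 1:1 allocation ratio".

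For haemoglobin, 208 is said to "provide 90% probability that, if the real group difference in haemoglobin concentration is 5.0 g/L or more". The event to which this probability refers is that "the 95% CI for the difference would exclude 0". The assumed SD is 10 g/L in each group.

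For ferritin the probability is again 90%. The effect is a 75% higher geometric mean in the haem group than in the control group, and the variance of the natural log of ferritin is given as 1.232 in each group. The criterion is that "the 95% CI for the ratio would exclude 0". The text below Fig. 2 puts the effect in absolute terms as a rise from 13.4 to 23.4 μg/L.

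**The concern.** Two things in this section look wrong.

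1. **Null value.** Zero is the no-effect value for a difference, for a log ratio and for a percentage change. It is not the no-effect value for a ratio, which is 1. An interval for a ratio of geometric means, back-transformed from the log scale, is positive at both ends whatever the data. The printed criterion is therefore met with certainty, and a 90% probability attached to it has no meaning.

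2. **Size against power.** The section prints every input that a two-group calculation needs, and those inputs do not give 208 for either endpoint. Either an input that is not stated was used, or a stated one is wrong. The possible explanations differ in consequence: some leave ferritin with power to spare, and one puts it just under the stated 90%.

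**Working it through.** **Inputs, all from the article.** Two-sided 95% CI (z = 1.960); 90% power (z = 1.2816); 1:1 allocation; 5% loss. Haemoglobin: difference 5.0 g/L, SD 10. Ferritin: ratio 1.75, so ln 1.75 = 0.5596; log variance 1.232, so SD = √1.232 = 1.110. The absolute figures agree with a multiplicative effect: 23.4/13.4 = 1.746.

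**Attempt to reproduce 208.** n per arm = 2 × variance × (1.960 + 1.2816)² / δ², with (1.960 + 1.2816)² = 10.507.

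- Haemoglobin: 2 × 100 × 10.507 / 25 = 84.06, so 85 per arm and 170 evaluable; 170/0.95 = 178.9, so 179 randomised.
- Ferritin: 2 × 1.232 × 10.507 / 0.5596² = 82.67, so 83 per arm and 166 evaluable; 166/0.95 = 174.7, so 175 randomised.

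Using the t distribution (86 and 84 per arm) and rounding up within each arm after loss gives at most 182 and 178. The ranges are thus 179–182 for haemoglobin and 175–178 for ferritin. The figure of 208 is 14% (208/182) to 19% (208/175) higher and is not reproduced.

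**Power that 208 delivers.** Evaluable: 208 × 0.95 = 197.6, or 98.8 per arm. Power = Φ(δ / (SD × √(2/98.8)) − 1.960).

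- Haemoglobin: Φ(3.514 − 1.960) = 94.0%.
- Ferritin, variance 1.232: Φ(3.544 − 1.960) = 94.3%.

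**Which changed input would lead to about 208?**

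| Changed reading | Per arm | Total | Conflict with the text |
|---|---|---|---|
| Ferritin, 1.232 is an SD, or the variance is 1.23² | 102 | 204 before loss; 215–216 after | Printed as a variance of 1.232; exceeds 208 once loss is added |
| 95% power, no loss | 104 (haemoglobin), 103 (ferritin) | 208, 206 | Text says 90% power and 5% loss |
| 97.5% CI for each endpoint | 100 (haemoglobin), 98 (ferritin) | 211, 207 after loss | Text says 95% CI for both |

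Under the first reading, ferritin power at 98.8 per arm is Φ(3.193 − 1.960) = 89.1% with SD 1.232, and 89.2% with SD 1.23.

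Each row contradicts something printed, and nothing in the article shows which, if any, was used.

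**The case against.** **The sentence is not a decision rule.** A reader might infer that one of the two primary endpoints has a success threshold that cannot fail. The article does not support that. The sentence describes what the calculation was meant to achieve. Statistical analysis {20a} specifies linear regression, with transformation where necessary, and effects reported with 95% CIs; nothing there tests a ratio against 0. The log-scale variance, and the correct use of 0 for the haemoglobin difference, point to a slip of wording. This objection stands, and it confines the error to the sample-size statement.

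**208 is still enough.** The article claims only that 208 suffices for 90%, and on the printed inputs it gives more. A reader might infer an underpowered trial; the figures show the opposite. This also stands. But the section says that these endpoints determined the size, and gives no reason for 26 to 33 children beyond what the inputs require. Fig. 2, which shows sizes for several effect sizes, is not available here and may hold the explanation. It could not make the printed inputs yield 208.

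**A 97.5% interval for each endpoint.** A reader might take the near-match as evidence that the trial was sized with a correction for two endpoints. That is conjecture: the section gives 95% for both endpoints and mentions no split of alpha. With consistent rounding up, the totals are 211 and 207, so haemoglobin would need slightly more than 208.

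**Restating 94% for both endpoints.** This would be safe only if 1.232 is a variance. The figure comes from a cited study that is not available here. If it is an SD, or a variance of 1.23 squared, 94% would be wrong for ferritin.

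**Conclusion.** Both parts hold within these limits. The null value printed for the ferritin ratio is wrong and should be 1. The printed size and power do not match: the inputs require about 179–182 children for haemoglobin and 175–178 for ferritin, and 208 with 5% loss gives about 94% power for each.

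The haemoglobin result rests only on printed inputs. The ferritin result depends on 1.232 being the variance, as printed; otherwise its power is about 89%, just below the stated 90%. All figures are for an unadjusted comparison of two groups, because the article states no baseline correlation from which to credit the planned baseline adjustment.

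These are errors in the justification of the sample size. They do not affect the analysis, and on the inputs as printed the size is conservative.

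**What to change.** - In Sample size determination {14}, say that the 95% CI for the ferritin ratio would exclude 1 or, equivalently, that the CI for the log ratio would exclude 0.
- Check the source of 1.232 and state whether it is a variance, an SD, or 1.23 squared.
- Restate the power of 208 with 5% loss at the 95% CI: about 94% for haemoglobin; for ferritin, about 94% if 1.232 is the variance, or about 89% if it is an SD or 1.23 squared.
- If 208 was reached with another CI level, power or loss allowance, state it and show the calculation.

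The cost is one look at the source and a few changed words and figures. The number enrolled and the analysis stay as they are.

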**Fig. 2 Fig2:**
[figure not shown]
Sample size requirements for various intervention effect size

In absolute terms, an effect of 75% change in serum ferritin concentration would correspond to an increase in the geometric mean value from 13.4 μg/L [estimate obtained from Gambian children with similar age range in a previous study [15]] to 23.4 μg/L (difference, 10 μg/L).

#### Statistical analysis {20a}

Statistical analysis will be conducted using the R Studio (R-4.3.3; https://cran.r-project.org/) and STATA software (vs 18; StataCorp, College Station, TX, USA). The intervention groups will be characterised at baseline and end survey using conventional summary statistics such as prevalence, means or counts with standard deviations (SDs), geometric means (geometric SDs) or medians with 25th and 75th centiles, as appropriate. We will report the baseline characteristics as detailed in Table 2. Linear regression will be employed for analysing continuous outcomes, with transformations applied when necessary. Tobit regression will be done for censored variables. Binomial and logistic regression will be used to analyse binary outcomes. Other types of analysis including generalised regression models or non-parametric analysis may be considered for variables that do not follow a log-normal distribution.

**Table 2 Tab2:** Characteristics of the study population at baseline (intention-to-treat population)

Baseline variable	Haem iron	Ferrous sulphate
*n*, as randomised	*n*	*n*
Age, months	–	–
Sex (male/female)	–	–
Number of live children born to the mother	–	–
Serum iron, μmol/L	–	–
Serum ferritin, μg/L	–	–
Serum soluble transferrin receptor, mg/L	–	–
Serum sTfR/log_10_(ferritin) index	–	–
Serum transferrin, g/L	–	–
UIBC, μmol/L	–	–
TSAT, %	–	–
Haemoglobin, g/dL	–	–
MCV, fL	–	–
MCH, pg	–	–
MCHC, g/dL	–	–
Reticulocyte count, × 10^9^/L	–	–
Reticulocyte count	–	–
Immature reticulocyte fraction	–	–
Reticulocyte haemoglobin, pg	–	–
Serum hepcidin, μg/L	–	–
Serum erythropoietin, IU/L	–	–
Serum *α*_1_-acid glycoprotein, g/L	–	–
Serum erythroferrone, μg/L	–	–
Below or equal to LOQ (≤ 0.16 μg/L)	–	–
Serum C-reactive protein	–	–
Below or equal to LOQ (≤ 0.60 mg/L)	–	–
Height-for-age *z*-score, SD	–	–
Weight-for-age *z*-score, SD	–	–
Weight-for-height *z*-score, SD	–	–

Values indicate *n*, mean (SD); *n*, geometric mean (geometric SD); *n* (%), prevalence; *n*, median (25 and 75% percentiles)

*LOQ* limit of quantification, *MCH* mean corpuscular haemoglobin, *MCHC* mean corpuscular haemoglobin concentration, *MCV* mean corpuscular volume, *sTfR* soluble transferrin receptor, *TSAT* transferrin saturation, *UIBC* unsaturated iron-binding capacity

The primary analysis concerns the effects of the intervention on haemoglobin concentration and serum ferritin concentration at day 84 after the start of the intervention (day 0), adjusting for the same variable measured at baseline. The analysis will be based on a modified intention-to-treat approach, including all randomised children who received at least one supplemental dose. Effect sizes will be reported with 95% CIs as detailed in Table 3.

**Table 3 Tab3:** Effect of iron supplementation on primary and secondary outcomes (intention-to-treat population)

Outcome variable	Haem iron	Ferrous sulphate	Group difference, unadjusted (95% CI)	*p*-value	Group difference, adjusted (95% CI)	*p*-value
Serum iron, μmol/L	–	–	–	–	–	–
Serum ferritin, μg/L	–	–	–	–	–	–
Serum soluble transferrin receptor, mg/L	–	–	–	–	–	–
Serum transferrin, g/L	–	–	–	–	–	–
UIBC, μmol/L	–	–	–	–	–	–
TSAT	–	–	–	–	–	–
Serum sTfR/log_10_(ferritin) index	–	–	–	–	–	–
Haemoglobin, g/dL	–	–	–	–	–	–
Anaemia (haemoglobin < 11.0 g/dL)	–	–	–	–	–	–
MCV, fL	–	–	–	–	–	–
MCH, pg	–	–	–	–	–	–
MCHC, g/dL	–	–	–	–	–	–
Reticulocyte count, × 10^9^/L	–	–	–	–	–	–
Reticulocyte count, %	–	–	–	–	–	–
Immature reticulocyte fraction, %	–	–	–	–	–	–
Reticulocyte haemoglobin, pg	–	–	–	–	–	–
Serum hepcidin, μg/L	–	–	–	–	–	–
Serum erythropoietin, IU/L	–	–	–	–	–	–
Serum erythroferrone, μg/L	–	–	–	–	–	–
Serum C-reactive protein, mg/L	–	–	–	–	–	–
Serum *α*_1_-acid glycoprotein, g/L	–	–	–	–	–	–
Height-for-age *z*-score, SD	–	–	–	–	–	–
Weight-for-age *z*-score, SD	–	–	–	–	–	–
Height-for-weight *z*-score, SD	–	–	–	–	–	–

In secondary analyses, we will adjust intervention effects for sex, age, haemoglobin concentration and serum concentrations of ferritin and soluble transferrin receptor at baseline (continuous variables except sex). Fractional polynomial regression analysis will be utilised to explore the relationship between the magnitude of the intervention effect on haemoglobin levels and the baseline iron status.

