**Methods:**

This will be a two-arm, randomised controlled trial. Gambian children aged 6–12 months with anaemia will be recruited within a predefined geographical area and recruited by trained field workers. Eligible participants will be individually randomised using a 1:1 ratio within permuted blocks to daily supplementation for 12 weeks with either 10.0 mg of elemental iron as haem or ferrous sulphate. Safety outcomes such as diarrhoea and infection-related adverse events will be assessed daily by the clinical team (see [name] et al. Additional file 4_Adverse event eCRF). Linear regression will be used to analyse continuous outcomes, with log transformation to normalise residuals as needed. Binary outcomes will be analysed by binomial regression or logistic regression, Primary analysis will be by modified intention-to-treat (i.e., those randomised and who ingested at least one supplement dose of iron), with multiple imputations to replace missing data. Effect estimates will be adjusted for baseline covariates (C-reactive protein, alpha-1-acid glycoprotein, haemoglobin, ferritin, soluble transferrin receptor).

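### Adjustment for an outcome's own baseline is stated only for haemoglobin and ferritin; 17 of the 24 Table 3 rows, including hepcidin and growth, have no own-baseline term in any stated model, which loses precision but causes no bias

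*Protocol article*

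**What the plan says.** All statements are in the Protocol article.

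- **Statistical analysis {20a}, primary analysis.** "The primary analysis concerns the effects of the intervention on haemoglobin concentration and serum ferritin concentration at day 84", with the model "adjusting for the same variable measured at baseline". This is the only explicit own-baseline rule, and it is attached to these two endpoints.
- **Same section, further adjustment.** "In secondary analyses, we will adjust intervention effects for sex, age, haemoglobin concentration and serum concentrations of ferritin and soluble transferrin receptor at baseline".
- **Abstract, Methods.** "Effect estimates will be adjusted for baseline covariates (C-reactive protein, alpha-1-acid glycoprotein, haemoglobin, ferritin, soluble transferrin receptor", a list that differs from the one in the analysis section.
- **Same section, Table 3.** Each of 24 outcome rows has an unadjusted and an adjusted group difference. The table does not say what the adjusted column adjusts for in any row.
- **Same section, model type.** "Linear regression will be employed for analysing continuous outcomes, with transformations applied when necessary". Tobit regression is assigned to censored variables.
- **Availability of baselines.** Outcome measures {12}: "The primary and secondary outcomes will be collected at baseline (day 0) and endline (day 84) at the study sites". Laboratory and clinical evaluations {33} has "anthropometric measurements (weight and height at baseline and endline". Table 2 lists the baseline markers and z-scores ("We will report the baseline characteristics as detailed in Table 2").

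**The concern.** When the same variable is measured in the same child before and after treatment, its baseline is usually the best single predictor of its endline value. Leaving it out keeps between-child variance in the comparison that the data could remove. It also carries any chance baseline imbalance in that variable into the day-84 difference.

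The outcomes affected are not trivial. Growth is a named outcome, and hepcidin is central to the rationale in the Background. For the growth z-scores the listed covariates are weak substitutes: age and sex are already largely standardised out of a z-score, and haemoglobin, ferritin and sTfR are haematological and iron markers. A null result on growth or hepcidin would be less informative than the same children could make it.

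**Working it through.** **Step 1. Which Table 3 rows have their own baseline in a stated model?**

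| Coverage | Rows | Count |
|---|---|---|
| Own baseline named in the analysis section | Haemoglobin, ferritin, sTfR | 3 |
| Covered through components in that list | sTfR/log ferritin index, anaemia | 2 |
| Covered by the Abstract list only | CRP, AGP | 2 |
| In no stated model | Serum iron, transferrin, UIBC, TSAT, MCV, MCH, MCHC, reticulocyte count (absolute and %), immature reticulocyte fraction, reticulocyte haemoglobin, hepcidin, erythropoietin, erythroferrone, three growth z-scores | 17 |

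The total is 3 + 2 + 2 + 17 = 24. If only the analysis section's list applies, CRP and AGP also lose theirs and the count becomes 17 + 2 = 19.

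**Step 2. Are the baselines available?** Yes. All 17 appear in Table 2.

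**Step 3. How much precision is at stake?** The plan gives no precision or power figure for these outcomes, so there is none to reproduce.

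Inputs:
- 208 randomised 1:1 with 5% dropout (Study design; Sample size determination {14}), so evaluable per arm n = 208 × 0.95 / 2 = 98.8.
- Baseline-to-day-84 correlation ρ: not in the document. Assumed range 0.3 to 0.9.

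Formulas:
- Half-width without own baseline: 1.96 × √(2/98.8) = 0.279 SD.
- Half-width with own baseline: 0.279 × √(1 − ρ²).
- Total to randomise for the same precision without it: 208 / (1 − ρ²).

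| ρ (assumed) | 1 − ρ² | SE ratio | Half-width, SD | Equivalent total |
|---|---|---|---|---|
| 0 | 1.00 | 1.000 | 0.279 | 208 |
| 0.3 | 0.91 | 0.954 | 0.266 | 229 |
| 0.5 | 0.75 | 0.866 | 0.242 | 277 |
| 0.7 | 0.51 | 0.714 | 0.199 | 408 |
| 0.9 | 0.19 | 0.436 | 0.122 | 1095 |

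Against the unadjusted comparison, ρ is the simple correlation and SD is that of the outcome. Against a model that already holds the listed covariates, ρ is the partial correlation and SD is the residual SD from that model.

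**Step 4. How much is left once the listed covariates are in?** The SE ratio is √[(1 − R² with own baseline) / (1 − R² of listed covariates)]. The R² values are again assumptions.

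| R², listed covariates | R², with own baseline | SE ratio |
|---|---|---|
| 0.10 | 0.25 | √(0.75/0.90) = 0.913 |
| 0.10 | 0.49 | √(0.51/0.90) = 0.753 |
| 0.10 | 0.64 | √(0.36/0.90) = 0.632 |
| 0.20 | 0.25 | √(0.75/0.80) = 0.968 |

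So the gain runs from about 3% of the standard error (iron-related rows largely explained by baseline haemoglobin, ferritin and sTfR) to well over a third.

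**The case against.** The strongest reply is that the text is silent rather than wrong. The sentence on further adjustment speaks of secondary analyses, not secondary outcomes. It follows the primary analysis, and the next sentence concerns haemoglobin. It may therefore describe a further-adjusted model of the two primary endpoints, with the covariates for other outcomes left to the SAP. The adjusted column of Table 3 could then mean own-baseline adjustment in every row.

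That reading is possible, so one cannot say that the protocol rules own-baseline adjustment out. But nothing in the document extends the rule beyond haemoglobin and ferritin, while it does name two covariate lists and an adjusted column for all 24 rows. On either reading the column needs a definition, and the same sentence supplies it.

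Three other replies stand:

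- A reader might infer that haemoglobin and ferritin alone are ever adjusted for their own baseline. That goes too far: sTfR is in both lists, its ferritin index and anaemia are covered through their components, and the Abstract adds CRP and AGP.
- The size rests on correlations that the document does not supply. It also states no target effect for these outcomes, so no power loss can be attributed to them without a second assumption.
- Randomisation keeps the comparison valid without the baseline term.

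**Conclusion.** The point holds as one of efficiency for non-primary outcomes. In 17 of 24 Table 3 rows no stated model contains the outcome's own baseline, although it is measured. With about 99 evaluable children per arm, adding it would shorten the 95% CI half-width from 0.28 SD to about 0.27 SD at ρ = 0.3 and 0.12 SD at ρ = 0.9, with smaller gains where the listed iron markers already account for much of the outcome. The same child's z-score 12 weeks earlier may well correlate strongly with the endline value, but the document gives no figure, so the range is all that can be claimed.

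A reader might go further and infer biased results or a weakened primary analysis. The documents do not support either: allocation is randomised, and both primary endpoints are adjusted for their own baselines.

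**What to change.** In Statistical analysis {20a}, define the adjusted column of Table 3, for example:

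*For every continuous outcome measured at day 0, the adjusted group difference at day 84 comes from the linear or Tobit model specified for that outcome, with its own baseline value on the same transformation as a covariate, plus any further listed covariates.*

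With it:

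- Reconcile the covariate lists in the Abstract and in the analysis section.
- Apply the same rule to faecal calprotectin as a separate safety outcome. It is collected at baseline and endline but has no row in Table 3.
- For markers with values at or below the LOQ (Table 2 names CRP and erythroferrone), enter the baseline with a below-LOQ indicator.
- For missing baselines, use a missing indicator. The imputation in section {20c} is described for the primary analysis, and its model leaves out censored and derived variables, so it cannot be relied on here.

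The cost is a few lines of text and usually one or two degrees of freedom per model (the baseline value, and an indicator where one is needed), out of about 198 evaluable children. No new data or visits are required.
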